#### The Mobile Health Antiretroviral Therapy Adherence App (Fitbit Plus)

An earlier version of Fitbit Plus (previously known as Twine) was found to show promise in improving ART adherence [25]. Fitbit Plus is fully Health Insurance Portability and Accountability Act compliant. The participant version of Fitbit Plus runs on an iPhone with iOS version 9.0+ or an Android phone with version 4.4+. The vast majority (94%) of smartphones in the United States use a platform (iOS or Android) that is compatible with Fitbit Plus [30]. Therefore, the proposed intervention could be disseminated readily. In addition to running on smartphones, the health coach version also runs on a Chrome, Firefox, or Safari Web browser or an iPad with iOS version 9.0+. The Fitbit Plus app that is compatible with any medication, includes medication reminders and tracking, and secure 2-way messaging. Fitbit Plus will generate a push notification at the time ART dosing should occur each day. After each push reminder, participants are prompted to click *yes* or *no* that they have taken their medication. Responding to the prompt requires only the single click of a text box, minimizing respondent burden.

On their “dashboards,” health coaches will be able to monitor participants’ adherence to ART in real time and identify participants whose adherence falls below optimal levels and may be in need of support, in addition to responding to participant requests for support or information. There is general support in the extant ART adherence literature for adherence monitoring and feedback [31,32]. Health coaches will support ART adherence through interactive secure messaging. Health coaches will provide support, encouragement, and resources, including links and attachments, via the messaging feature. At a minimum, health coaches will message participants at least weekly. In the development phase of the project, we will develop content that health coaches can send via the app to address commonly encountered situations that impede ART adherence (eg, stress/anxiety, depressive symptoms, substance use, and treatment fatigue). Coaching materials and strategies will also be refined based on pilot participant feedback. Fitbit Plus will allow us to examine utilization data for both the adherence tracking and interactive features.

#### Training and Supervision of Health Coaches

Health coaches will receive training and supervision in the face-to-face intervention and the interactive coaching component of the mHealth ART adherence app from the first author who has extensive experience in the training, supervision, and delivery of interventions grounded in motivational interviewing and CBT. Training will include didactics, role-playing, and review of audiotaped sessions. Weekly supervision will be held to ensure competent and standardized delivery. All face-to-face sessions will be audiotaped, and the content of the interactive coaching messages delivered via Fitbit Plus will be logged. A randomly selected 30% (18/60) of face-to-face session recordings and Fitbit Plus coaching messages will be rated for health coach competence and adherence to intervention protocol.

### Phase 2: Randomized Controlled Trial Phase

#### Procedures

After informed consent has been obtained, participants will complete a baseline interview (see Table 1 for timeline of procedures). EPBs will be distributed at the conclusion of the baseline interview, with instructions to begin storing their ART medication in the EPB and to continue to adhere to their regimen as they normally would. Adherence will then be monitored for a 2-week period to establish a baseline adherence level. Participants will be randomized to Fitbit Plus or SOC using urn randomization [33] to ensure that the 2 groups are comparable on important prognostic variables (number of years on ART, percent self-reported adherence on the visual analog scale [26], level of substance use reported on the Timeline Followback (TLFB) interview [34], and level of depressive symptoms reported on the Centers for Epidemiologic Studies-Depression Scale [35]). Participants assigned to the Fitbit Plus condition will receive the face-to-face intervention followed by 12 months of access to Fitbit Plus, whereas the SOC condition will receive the face-to-face session alone. Participants will be informed whether or not they are receiving the app during the face-to-face session, and only Fitbit Plus participants will receive an introduction to the app. Follow-up interviews will be conducted 1, 3, 6, and 12 months after the baseline interview. Participants in phase 2 will be compensated US $25 for completion of the baseline interview and US $30, US $35, US $40, and US $50, respectively, for completion of the 1-, 3-, 6-, and 12-month follow-ups.

#### Measures

All data collection will be captured with a secure electronic data capture system developed by Vanderbilt University, REDCap. Paper versions of the assessments can be provided upon request but then will be entered by research staff into REDCap (see Table 2 for schedule of assessments).

**Table 1 table1:** Timing of participant enrollment, receipt of interventions, and assessment activities during phase 2.

Timepoint		Enrollment (–t1)	Baseline (0)	Intervention start (+2 weeks)	Post allocation			
					+1 month	+3 months	+6 months	+12 months
**Enrollment**								
	Eligibility screen	✓^a^	—^b^	—	—	—	—	—
	Informed consent	✓	—	—	—	—	—	—
	Allocation	—	✓	—	—	—	—	—
**Interventions**								
	Fitbit Plus	—	—	✓	✓	✓	✓	✓
	Standard of care	—	—	✓	—	—	—	—
**Assessments**								
	Primary outcomes	—	✓	—	✓	✓	✓	✓
	Secondary outcomes	—	✓	—	✓	✓	✓	✓
	Other outcomes	—	✓	—	✓	✓	✓	✓

^a^Indicates study activity will occur at the corresponding time-point.

^b^Not applicable.

**Table 2 table2:** Schedule of assessments.

Measures		Baseline	1-month follow-up	3-month follow-up	6-month follow-up	12-month follow-up
**ART^a^ adherence**						
	Electronic pill box data	✓^b^	✓	✓	✓	✓
	Adult AIDS Clinical Trials Group medication questionnaire	✓	✓	✓	✓	✓
	3-item ART adherence questions	✓	✓	✓	✓	✓
Viral load		✓	—^c^	—	✓	✓
**Potential treatment mechanisms**						
	LifeWindows information-motivation-behavioral skills ART questionnaire	✓	✓	✓	✓	✓
	HIV Treatment Adherence Self-Efficacy Scale	✓	✓	✓	✓	✓
**Potential moderators of treatment effects**						
	Timeline Followback	✓	✓	✓	✓	✓
	Center for Epidemiological Studies-Depression Scale	✓	✓	✓	✓	✓
	Fägerstrom Test for Nicotine Dependence	✓	✓	✓	✓	✓
**Treatment received**						
	Treatment services review	✓	✓	✓	✓	✓
	Use of medications	✓	✓	✓	✓	✓
**Feasibility and acceptability**						
	Fitbit Plus satisfaction questionnaire	—	—	—	✓	✓
	Semistructured interview	—	—	—	—	✓

^a^ART: antiretroviral therapy.

^b^✓ indicates measure will be administered at the corresponding time-point.

^c^Not applicable.

#### Antiretroviral Therapy Adherence

##### MEMS Cap

ART adherence will be measured via EPB throughout the course of the study. Participants will be asked to bring the EPB to each follow-up interview. At each follow-up interview, adherence data (dates and times of pill bottle openings) will be downloaded from the EPB and then returned to the participant for continued medication adherence monitoring. At the last study visit (12-month follow-up), EPBs will be collected from participants, and all data will be downloaded and then deleted from the device.

Although this is an objective measure of adherence, there are limitations that should be noted. As the data from most EPBs must be downloaded using a specific device, there is a potential for data loss if a participant never brings the EPB to a study visit or misplaces it entirely. We will attempt to mitigate this in the following ways: (1) by reminding participants to bring the cap to every visit and (2) having replacements available should a participant report misplacing their EPB. These strategies have successfully minimized data loss in previous longitudinal studies of medication adherence [36-39].

In addition, adherence rates may be artificially inflated as EPBs record the date and time every time it is opened. It does not differentiate purposes for opening (eg, taking medication vs refilling pill bottle). EPBs could also potentially underestimate adherence rates owing to situations in which participants open the device, take out multiple doses, and then do not open the device again for several days but still take their medication (eg, pocketing doses for weekend travel). At each study appointment, participants will be asked if they can recall any instances in which they (1) opened the EPB but did not take medication or (2) took their medication but did not open the EPB. This information will be added to the EPB data to create a self-report corrected version of the EPB data. As is typically done in ART adherence studies (eg, [40]), we will consider the self-report corrected EPB data to be the primary ART adherence data. However, we will also conduct our planned data analyses on the uncorrected EPB data to bolster our confidence in the findings.

#### Self-Reported Adherence

Self-reported adherence will be collected at baseline and follow-up interviews using the Adult AIDS Clinical Trials Group medication questionnaire that asks participants to report on the number of doses missed of their prescribed ART within the last 4 days [41]. We will also assess self-reported adherence with a 3-item ART adherence measure developed by Wilson and colleagues [42]. This brief measure has been found to have good psychometric properties and good construct validity when compared with electronic drug monitoring [42].

#### Viral Load

Viral load data will be collected at baseline and at the 6- and 12-month follow-up appointments. These data will be collected through a laboratory belonging to a hospital system in the Northeastern region of the United States. The laboratories use assays with sensitivity to detect viral load >20 copies/mL.

#### Potential Treatment Mechanisms

A total of 2 factors that may be mechanisms of successful treatment for improving ART adherence are motivation and self-efficacy. The LifeWindows IMB ART Adherence Questionnaire (LW-IMB-AAQ) [43] is designed to measure barriers to ART adherence that fall within the information, motivation, and behavioral skills areas. These areas are consistent with the IMB model of adherence [13]. Self-efficacy for adherence to HIV medications will be assessed using the HIV Treatment Adherence Self-Efficacy Scale (HIV-ASES), which has been shown to have robust internal consistency and reliability [44]. The HIV-ASES is a 12-item scale of patient confidence in their ability to carry out behaviors related to adhering to medication regimens. Responses range from 1 (“cannot do it at all”) to 10 (“completely certain can do it”). Item scores are averaged, with higher scores indicating higher adherence self-efficacy. The LW-IMB-AAQ and HIV-ASES will be administered at the baseline and follow-up interviews.

#### Potential Moderators of Treatment Effects

There are well established links between substance use, depressive symptoms, and poor ART adherence among PLWH [45-47]. Therefore, we will evaluate whether substance use and/or depressive symptoms moderate treatment effects. The TLFB interview will be administered to assess daily alcohol and drug use at baseline, as well as during the follow-up interviews. The TLFB interview is a calendar-assisted structured interview that provides a way to cue memory so that accurate recall of prior substance use is enhanced [48,49]. The TLFB interview has excellent reliability [50] and validity [48] and will provide data on the number of standard drinks consumed per day and types of drug classes used each day. At baseline, it will be administered to assess substance use during the 3 months before the interview. The Center for Epidemiological Studies-Depression Scale [35] will be used to measure level of depressive symptoms at baseline and follow-up interviews. This 20-item measure is widely used and has good sensitivity and specificity and high internal consistency [51]. Finally, nicotine dependence has also been associated with poor ART adherence [52,53]; thus, we will collect information about nicotine dependence during the baseline and follow-up interviews with the widely used Fägerstrom Test for Nicotine Dependence [54].

#### Treatment Received

The Treatment Services Review (TSR) [55] will be used to assess receipt of case management, psychiatric, substance use, and other treatment services. At baseline, participants will be asked about services received in the previous 3 months. At follow-up interviews, they will be asked about services received since the previous interview. We will modify the TSR to ask specifically about HIV-related services received, including medical treatment for any ART-related side effects or HIV-related sequelae. Participants will also be asked to provide information regarding the use of medications for medical, psychiatric, or substance use indications. At baseline, patients will be asked to provide information regarding medications used in the past 3 months. At each follow-up interview, they will be asked to provide information concerning use of medications since the previous interview.

#### Feasibility and Acceptability

At the conclusion of the study, we will compile a patient eligibility rate, enrollment refusal rate, rate of recruitment, and follow-up completion rate to evaluate the feasibility of conducting a subsequent larger scale study using this protocol. We will also compile a study dropout rate and intervention session completion rate as indices of acceptability. Intervention acceptability and feasibility will also be assessed by asking participants randomized to receive Fitbit Plus satisfaction questions at the 6- and 12-month follow-ups. These questions will allow us to collect participants’ overall opinions of the smartphone app and will allow us to observe whether satisfaction changes between 6 and 12 months. In addition, a semistructured interview will be completed with these participants at the 12-month follow-up to solicit additional information about the acceptability and feasibility of the intervention. More specifically, the semistructured interview will allow us to ask questions about different features of the app, what their favorite and least favorite aspects were, and if they have any recommendations for improvement.

### Planned Analyses

Tests of the effects of treatment on the primary outcome variable (percent ART adherence based on corrected EPB data at 1-, 3-, 6-, and 12-month follow-ups) will be conducted using a fractional logit model [56] estimated by generalized estimating equations (GEEs) [57-59]. GEE is a quasi-likelihood estimation method of repeated measures analysis that allows for the inclusion of both categorical and continuous independent variables and for appropriate modeling of covariance structures when outcomes are correlated across time. The primary, between groups, independent variable in the above regression analysis is treatment group assignment. Variables measured at baseline will be examined using screening runs before primary analyses to see which of these baseline variables are most strongly associated with the primary outcome (adherence based on EPB data) in our sample. Those that show significant relationships with outcome will be entered as additional covariates in the primary analyses. The linear effect of time will also be included as a covariate in these analyses, as we assume that adherence rates will show a tendency to decrease over time. We will also test for nonlinear (ie, higher order) effects of time. Testing the time by group interaction will indicate the extent to which treatment differences are more or less pronounced closer in time to the intervention.

The same process described above for EPB adherence data will be employed to examine the impact of Fitbit Plus, relative to SOC, on the secondary measures of self-reported adherence percentage and viral load (dichotomized). Changes in viral load test assays have created inconsistencies in the literature in regard to level of viral load that is detectable. To be able to compare our results with the extant literature, we will dichotomize viral load at the 3 most commonly used levels (20, 50, and 200 copies/mL) and examine intervention effects using each of these levels. We will then explore potential mediators (motivation and self-efficacy) of the intervention effect on HIV medication adherence. This will be done using 2 common approaches to evaluating mediation mechanisms; Baron and Kenny’s approach [60] and structural equation modeling [61,62].

In addition to the analyses that address the specific aims of the study, our data set will allow us to perform exploratory analyses that could enhance our understanding of ART adherence and may suggest avenues for future research. We will examine the temporal association between alcohol and drug use (TLFB) and missed ART doses. Using hierarchical linear models, we will regress daily ART adherence (based on EPB data) onto daily substance use. This will allow for the calculation of odds ratios that reflect the extent to which alcohol and drug use on a given day are associated with ART adherence on that day, relative to days in which participants refrained from using substances. Given that ART adherence will be examined dichotomously for these analyses, a logistic regression model will be specified in all analyses. More fine grained analyses will allow us to examine whether certain classes of drugs or level of alcohol consumption are temporally associated with missed ART doses.

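### Baseline adherence and the four urn-balancing variables enter the primary model only if they pass a significance screen on the trial's own outcome data; they should be prespecified

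*Protocol article*

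**What the plan says.** All references are to the protocol article.

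- **Outcome.** Planned Analyses defines the primary outcome as "percent ART adherence based on corrected EPB data at 1-, 3-, 6-, and 12-month follow-ups". Baseline pill-box adherence is therefore not part of the response vector.
- **Terms fixed in the model.** Two are named: "The primary, between groups, independent variable in the above regression analysis is treatment group assignment" and "The linear effect of time will also be included as a covariate in these analyses". Higher-order time and the time-by-group interaction are to be tested.
- **Other covariates.** "Variables measured at baseline will be examined using screening runs before primary analyses", to see which are most strongly related to the primary outcome in the sample. Then "Those that show significant relationships with outcome will be entered as additional covariates in the primary analyses". The significance level is not given, nor whether the screen is univariable or multivariable.
- **Baseline adherence.** Under Phase 2, Procedures: "Adherence will then be monitored for a 2-week period to establish a baseline adherence level". Table 2 lists pill-box data at baseline.
- **Allocation.** The same section allocates "using urn randomization [33] to ensure that the 2 groups are comparable on important prognostic variables". The four are years on ART, self-reported adherence on the visual analog scale (VAS), substance use on the Timeline Followback (TLFB), and depressive symptoms on the CES-D.

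No section says that any of these five variables enters the model regardless of the screen.

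**The concern.** The trial spends two weeks measuring each participant's baseline value of the primary outcome and builds its randomization on four variables that it regards as prognostic. The analysis then makes adjustment for all five depend on a p-value in the same 53 to 60 people. Three things are at stake:

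- **Precision.** A prognostic variable that narrowly misses significance is left out, and noise variables that reach significance by chance go in.
- **Standard errors.** Balancing on a variable without adjusting for it leaves the model-based standard error somewhat too large.
- **A stable target.** The logit coefficient is non-collapsible: its value depends on which covariates are in the model. The Discussion wants an effect size stable enough to justify a larger trial, and a data-selected covariate set works against that. The same process is applied to self-reported adherence and to viral load at three cut-points, so each model may end up with a different set.

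**Working it through.** **Inputs from the article:** 60 planned for phase 2 (Participants and Recruitment), 53 randomized so far (Results), four urn variables and one 2-week baseline adherence measure (Phase 2, Procedures). The article gives no power calculation, significance level for the screen or covariate-outcome correlation, so there is no stated figure to reproduce.

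**Assumptions:** a two-sided 5% screen and the correlations given below.

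**1. Chance of passing the screen.** By Fisher's z, P(pass) ≈ Φ(atanh(r)·√(n−3) − 1.96); the opposite tail is negligible.

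- r=0.25, n=60: 0.2554 × √57 = 1.928; Φ(−0.03) = 0.49.
- r=0.25, n=53: 0.2554 × √50 = 1.806; Φ(−0.15) = 0.44.

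The chance of being dropped at other values of r:

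| r | n=60 | n=53 |
|---|---|---|
| 0.2 | 67% | 70% |
| 0.3 | 35% | 41% |
| 0.4 | 11% | 15% |
| 0.5 | 1.4% | 2.7% |

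Four independent urn variables at r=0.25 and n=60 all pass with probability 0.49⁴ ≈ 0.06, so at least one is dropped about 94% of the time. That figure follows directly from the assumed r.

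**2. Chance that noise enters.** With k null candidates it is 1 − 0.95^k: 23% for k=5, 40% for k=10, 64% for k=20.

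**3. Screened against prespecified, linear stand-in for the GEE.** 6,000 runs, n=60, allocation balanced on four variables (r=0.25 each), baseline adherence r=0.5, ten null candidates.

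| | Unadjusted | Screened | Prespecified |
|---|---|---|---|
| Type I error | 3.5% | 4.1% | 4.6% |
| Power, true effect 0.60 SD | 63% | 82% | 88% |
| Mean estimate, true effect 0.60 SD | 0.60 | 0.57 | 0.60 |
| SD of estimate, true effect 0.60 SD | 0.239 | 0.193 | 0.188 |

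The variance ratio, screened to prespecified, is (0.193/0.188)² = 1.05. Under the null each urn variable was dropped in about 52% of runs and baseline adherence in 1.5%. A linear model is collapsible, so the fall from 0.60 to 0.57 is real attenuation.

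**4. Screened against prespecified, fractional logit.**

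- Four visits, GEE, urn variables at r about 0.25, baseline adherence at r about 0.69, 14 null candidates: power 62% screened and 66% prespecified at n=60, and 53% and 57% at n=48. With 1,000 runs each power has a Monte Carlo SE of about √(0.62×0.38/1000) = 1.5 points. Mean log-odds coefficients for one true effect were 0.44 unadjusted, 0.48 screened and 0.51 prespecified. Type I error was about 5% once standard errors were corrected.
- A separate set (2,000 runs per setting, n=53 and 60, 14 null candidates) gave a variance ratio of 1.00 to 1.01 with baseline adherence weighted 0.5 and 1.20 with it weighted 0.7. On the percentage-point scale the ratio was 1.03 to 1.24. Baseline adherence was dropped in 0 to 5% of runs, and attenuation was about 0.5 to 0.8 points on about 8.4.

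**The case against.** The strongest defence is that the rule is laid down in advance, selects on covariate-outcome association rather than on the treatment effect, and does little harm. Much of that stands. Type I error is not inflated. Baseline adherence, the most valuable covariate, will nearly always pass if it correlates with follow-up as one would expect. Whether the urn variables are usually dropped depends on r: at 0.4 they mostly survive. Part of the spread 0.44, 0.48, 0.51 is non-collapsibility, that is, different conditional estimands and not error. The Objective makes feasibility and acceptability primary, and the article concedes limited power, especially with multiple predictors.

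A reader might infer that the rule costs as much as about 50% more participants. The last simulated comparison of no adjustment with the fixed set gives SEs of 0.249 and 0.203, and (0.249/0.203)² = 1.50. The document does not support that reading: it plans screened adjustment, not an unadjusted model, and against the screened model the variance ratio is 1.00 to 1.24. A sample of 48 (53 × 0.90 = 47.7) is also pessimistic, because the 90% is 12-month follow-up and the GEE uses earlier visits too.

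The defence does not remove the point. An unseen analysis plan might hold more detail, but the article states a screening rule and exempts none of these variables from it.

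**Conclusion.** The point holds as a should-fix. Adjustment for baseline adherence and the urn variables is conditional on a significance screen, and with 53 to 60 participants a weakly to moderately prognostic urn variable has roughly an even chance of being left out. Relative to prespecification the cost is about 4 to 6 points of power and 0 to 24% in variance, with slight attenuation and no type I error inflation. The effect estimate also rests on a sample-dependent covariate set, which sits badly with the aim stated in the Discussion.

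These sizes rest on assumed correlations, an assumed 5% screening level and an assumed number of null candidates. A reader might go further and conclude that the efficacy result would be invalid or that baseline adherence would be lost; neither the text nor the calculations support that.

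**What to change.** Before data lock, replace the screening rule for the primary analysis with a named model: treatment, time, 2-week baseline pill-box adherence, years on ART, VAS adherence, TLFB substance use and CES-D. Use the same set for the secondary outcomes unless a reason is given. Keep any model with screened covariates as a labelled sensitivity or exploratory analysis. State which version of baseline pill-box adherence is used; the Measures section treats the self-report corrected data as primary. Reporting a marginal difference in percentage points alongside the logit coefficient is optional.

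The cost is wording and about five degrees of freedom. All five variables are already collected, although VAS adherence appears under screening and allocation and not in Table 2, so its source should be named. The Results section puts formal analysis after data collection ends, so by the article's own timeline the model can be fixed first.

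### The daily substance-use analysis is described as temporal but pairs use and dose only within the same day, so it cannot show order or next-day carry-over

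*Protocol article*

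**What the plan says.** The last paragraph of Planned Analyses in the protocol article states the aim of this exploratory work: "We will examine the temporal association between alcohol and drug use (TLFB) and missed ART doses". The model follows: "Using hierarchical linear models, we will regress daily ART adherence (based on EPB data) onto daily substance use". The resulting odds ratios are to show how far "alcohol and drug use on a given day are associated with ART adherence on that day", with the comparison made "relative to days in which participants refrained from using substances". The outcome is binary: "Given that ART adherence will be examined dichotomously for these analyses, a logistic regression model will be specified in all analyses". The finer analyses that the paragraph adds concern drug class and amount of alcohol. No lag is mentioned.

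The exposure is described under Potential Moderators of Treatment Effects: the Timeline Followback "will provide data on the number of standard drinks consumed per day and types of drug classes used each day". No time of day is mentioned. The pill box, by contrast, stores both the date and the time of each opening (MEMS Cap section).

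The MEMS Cap section also lists ways in which the box can miss doses that were taken, with "pocketing doses for weekend travel" as its example. It plans a correction from participants' recall at each appointment, treats the corrected data as primary, and repeats the planned analyses on the uncorrected data.

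**The concern.** A reader takes a temporal association to say something about sequence: use happens, then a dose is missed. Same-day pairing without clock times cannot say this. If someone takes a morning dose and drinks that evening, the dose is paired with drinking that came after it. Any effect of that drinking would fall on the next morning's dose, which is paired with the next day's use instead.

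Two things are at stake. A real carry-over effect could look weak or absent. A same-day odds ratio above 1 could also be read as showing order when it does not. The Discussion offers this analysis as an example of what the study will contribute, so how the result is labelled matters. Neither the primary outcome nor the comparison of Fitbit Plus with standard of care depends on it.

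**Working it through.** The article gives no odds ratio, power or rate of use for this analysis, so there is no figure of its own to reproduce. All inputs below are assumptions chosen to show direction and rough size.

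**1. A pure previous-day effect, by arithmetic.**

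Inputs: use on p = 25% of days; probability of a missed dose 0.20 if there was no use the day before; previous-day odds ratio 2.0; no same-day effect; lag-1 correlation of use r.

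- Miss probability after a use day: odds 2 × 0.20/0.80 = 0.50, so 0.50/1.50 = 0.333.
- P(use yesterday | use today) = p + r(1 − p).
- P(use yesterday | no use today) = p − rp.
- Miss probability today = 0.20 + 0.133 × P(use yesterday | today's status).

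| r | P(yesterday), use day | P(yesterday), non-use day | Miss, use day | Miss, non-use day | Same-day OR |
|---|---|---|---|---|---|
| 0 | 0.250 | 0.250 | 0.233 | 0.233 | 1.00 |
| 0.1 | 0.325 | 0.225 | 0.243 | 0.230 | 1.08 |
| 0.3 | 0.475 | 0.175 | 0.263 | 0.223 | 1.24 |
| 0.5 | 0.625 | 0.125 | 0.283 | 0.217 | 1.43 |

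**2. The same scenario by simulation.** With 53 people (the number enrolled in phase 2 according to Results), 365 days each, and person intercepts with SD 1, the same-day odds ratio is 1.05, 1.27 and 1.42 at r = 0.1, 0.3 and 0.5. This agrees with the table apart from sampling noise. With both days in the model, the previous-day odds ratio is 1.96 to 2.03 and the same-day odds ratio 0.98 to 1.02.

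A second simulation used 600 people, 360 days and Mantel-Haenszel odds ratios within person, with use on 50% of weekend days and 20% of weekdays. Its same-day odds ratio is 1.01 without day-to-day dependence and 1.24 with it. The previous-day odds ratio is 2.02 to 2.03.

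**3. A true same-day effect.** In the second simulation, with a same-day odds ratio of 2 and no lagged or weekend effect, the planned pairing returns 2.0.

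**4. Weekends.** Suppose use has no effect, the miss probability is 0.20, and a fraction f of taken weekend doses is recorded as missed. Then the recorded miss probability is 0.20 + 0.80 × f × P(weekend | use status).

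- f = 5%, use on 20% of weekdays and 40% of weekend days: P(weekend) is 0.8/1.8 = 0.444 on use days and 1.2/5.2 = 0.231 on non-use days. Misses are 0.2178 and 0.2092, giving an odds ratio of 1.05.
- f = 15%, use on 20% and 50%: P(weekend) is 1/2 = 0.50 and 1/5 = 0.20. Misses are 0.260 and 0.224, giving 1.22.
- As the second case, but with recall recovering half of the false misses (f = 7.5%): 0.230 and 0.212, giving 1.11.

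In the second simulation, stratifying by weekend brings odds ratios of 1.13 to 1.25 under no effect (weekend odds ratio for a miss 1.5 to 2) back to 0.99 to 1.01.

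**The case against.** The strongest reply is that the article defines its own target as use and adherence on the same day, speaks only of association, and makes no causal claim. The planned model estimates that target properly (step 3). A reader might infer that the odds ratio is uninformative about substance use and missed doses. The documents do not support this: what it lacks is order and carry-over, not all association.

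The dilution in steps 1 and 2 also follows from assuming that the whole effect falls on the next day. The article gives no dosing times; it says only that the app's reminder comes when a dose is due. For evening doses, use may well precede the dose on the same day, and same-day pairing is then apt. This stands. It is a reason to enter both days, not to put the lagged odds ratio first.

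A reader might also infer that the plan ignores weekends. That would be an inference from silence. The article lists no covariates for this model, and a condensed article commonly leaves them to the full protocol or analysis plan. Nor is the pocketing problem left unhandled, since the MEMS Cap section plans the recall correction and a repeat on uncorrected data. Advice on which version of the data to use would only restate that section.

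The reply does not remove the central point. The same-day pairing is written out, the exposure has no clock time, and the aim is called temporal.

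**Conclusion.** The point holds in a limited form. As specified, the analysis estimates day-level co-occurrence. It cannot show that use came before the missed dose, and it has no stated term for the next day's dose. Under an assumed previous-day odds ratio of 2.0 and no same-day effect, it would return about 1.0 to 1.4 for day-to-day correlations of use from 0 to 0.5. If the true effect lies within the day, nothing is lost.

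The weekend question is secondary. Recall at visits up to six months apart (6 to 12 months) may correct pocketed doses only in part. Any remaining inflation depends on use clustering at weekends, which is assumed here. The absence of a weekend term from the article is not an error.

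This is a minor improvement to an exploratory analysis that lies outside the specific aims.

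**What to change.** In the daily logistic mixed model, enter use on the previous day together with use on the same day as predictors of that day's dose. Report both odds ratios without ranking either first. If only the same-day term is kept, describe the result as a same-day association and drop the word temporal. Consider adding a weekend or day-of-week indicator.

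The cost is one or two extra model terms and no new data. The lag need not cost the first day: the boxes are handed out at the end of the baseline interview, and the baseline Timeline Followback covers the preceding 3 months, so use on the day before monitoring starts is already recorded. The Results section places formal analysis after the end of data collection, so the change can be fixed beforehand.
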